## Background

Hospital-treated DSH is common [1] and costly [2]. Repetition of DSH within 1 year of hospital admission occurs at a median proportion of 15% (interquartile range 12–25%) [1].

DSH is associated with a range of psychiatric issues [3], an increased risk of suicide attempts, and suicide [3, 4]. In Australia, DSH accounted for 6% of all hospitalised injury cases during 2012–2013 and four-billion dollars in healthcare expenditure annually, making prevention and early intervention an Australian national health priority [5]. Hospital-treated DSH predominantly includes deliberate self-poisoning (DSP) (approximately 90% of DSH cases) and other various methods, including, cutting, hanging, jumping, and burning [1]. Hospital-treated DSH is associated with an increased risk of suicide death, highlighting the importance of effective prevention and early intervention strategies.

BCIs, such as follow-up postcards, supportive letters, or phone calls have previously been shown to be associated with reductions in hospital re-presentation event rates. A recent systematic review and meta-analysis of BCIs for reducing DSH (letters, telephone calls and crisis “green cards”) found a non-significant benefit for any episode of repeat DSH (binary outcome) and a significant benefit for repetition event rates [6]. The individual studies identified in the systematic review and meta-analysis generally lacked statistical power and varied considerably in intervention timeframes and methodologies, highlighting the need for well-designed, large, RCTs to determine the efficacy of these BCIs.

SMS text messaging provides more immediate communication and may be a more effective intervention than postcards [6, 7]. Text messaging has been associated with positive outcomes for hospital patients in a pilot study [8] and in a prospective study [9]. These studies demonstrated the technical feasibility and acceptability of text messaging outreach in post-acute suicide attempters in different cultural contexts. Most participants considered the text message contacts an acceptable and useful form of help and indicated they wished to continue receiving those text messages.

If an SMS text messaging follow-up intervention is found to be effective in reducing DSH re-presentations, it would provide a lower-cost, higher coverage medical follow-up system than what has previously existed for this population.

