### Outcome measures

As primary endpoints, we will assess at 6 and 12-months post-index discharge, i) the number of hospital DSH re-presentations in each condition (repetition event rate) and ii) the time to first re-presentation in each condition. Secondary end-points include i) any DSH re-presentation, ii) suicide mortality, and iii) all-cause mortality. Mortality data will be obtained from routinely collected data sources available through NSW Health, other government agencies, and the Centre for Health Record Linkage (CheReL).

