### Sample size calculation

Assuming an incidence rate ratio (based on event rates) of RR = 0.66 [13] for the Intervention condition compared to TAU, with a 5% significance level, 80% power, and 10% adjustment for correlation of individuals within hospitals, a total sample size of 796 participants/subjects is required (398 participants in the Intervention condition and 398 subjects in the control condition). We have also assumed a median survival time (time to first repetition) in the TAU condition of 4.3 years. Currently ~ 15% in the usual care group who present for DSH re-present within the following 12-months, or a probability of survival of 0.85. Median survival (m) after 1-year (t) in the usual care group is t*log_e_(1/2)log_e_(*p* = 4.3 years). For assessing differences in median time to first repetition, assuming a median survival time in the usual care group of 73.5 days [12] and a similar relative difference in event rates between Intervention and TAU conditions as above (RR = 0.66), [13] the estimated median survival time in the Intervention condition is 121.8 days, which requires a total sample size of 138 participants/subjects (69 participants in the Intervention condition and 69 subjects in the TAU condition), with 5% significance and 80% power, and 10% adjustment for correlation of individuals within hospitals. The number of patients likely to die within the study period is very small. A previous longitudinal study in a similar Australian hospital setting [12] found a 1% suicide rate after 24 months and nearly a 2% suicide rate after 5 years.

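### The 138-patient calculation for time to first re-presentation uses a 73.5-day TAU median that cannot stand beside the 4.3-year median in the same paragraph; at the planned 796 patients, 12-month power is about 51%, not 80%

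*Protocol article*

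**What the plan says.** Under Outcome measures, time to first re-presentation is one of two primary endpoints: "As primary endpoints, we will assess at 6 and 12-months post-index discharge". The Abstract also limits the primary outcomes to 12 months from discharge.

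The Sample size calculation section first requires 796 patients (398 per arm) for the event-rate comparison, at a rate ratio of 0.66, 5% significance, 80% power and a 10% adjustment for hospital clustering. It continues: "We have also assumed a median survival time (time to first repetition) in the TAU condition of 4.3 years". The basis for that median is given directly: "Currently ~ 15% in the usual care group who present for DSH re-present within the following 12-months, or a probability of survival of 0.85".

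Later in the same paragraph comes a separate calculation for time to first repetition, "assuming a median survival time in the usual care group of 73.5 days", with the same ratio of 0.66. From this, "the estimated median survival time in the Intervention condition is 121.8 days, which requires a total sample size of 138 participants/subjects" (69 per arm), again at 5% significance, 80% power and a 10% adjustment.

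The Background section gives one-year repetition as a median of 15%, with an interquartile range of 12 to 25%.

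**The concern.** Two TAU medians about 21-fold apart are assumed for one quantity. The shorter one, which conflicts with the stated 15%, produces the only sample size the protocol gives specifically for time to first re-presentation. The power of a log-rank or Cox comparison depends on the number of events, so a median that makes nearly every patient an event greatly understates how many patients must be enrolled.

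The Intervention median also does not follow from the ratio said to generate it.

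At stake is the planning basis for the second hypothesis. Someone comparing 138 required with 796 planned could take this primary endpoint to have power to spare, and could read a null result in that light.

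**Working it through.** **Inputs from the protocol.** TAU 12-month repetition 15% (range 12–25%); TAU median 4.3 years or 73.5 days; Intervention median 121.8 days; ratio 0.66; 5% significance; 80% power; 10% adjustment; 138 or 796 patients, 1:1; horizon 12 months. **Assumed:** two-sided test (sidedness is not stated), proportional hazards, no loss to follow-up.

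**1. The 4.3 years.** ln(0.5)/ln(0.85) = 4.27 years. This agrees with 15% at 12 months.

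**2. What 73.5 days implies.** Under exponential survival, the proportion re-presenting by 12 months is 1 − 0.5^(365/73.5) = 96.8% under TAU. For 121.8 days it is 87.5%. The stated TAU figure is 15%.

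**3. Reproducing 138.** The implied ratio is 73.5/121.8 = 0.603. Events needed (Schoenfeld) are 4(1.96 + 0.84)²/(ln HR)² = 31.4/(ln 0.603)² ≈ 123, or 62 per arm. Then 62 × 1.1 = 68.2, rounded up to 69 per arm, or 138. Patients are set equal to events. Adding 24 months of accrual and 12 months of further follow-up with these medians gives 125.2 × 1.1 = 137.7, with 97% or more of each arm having an event. Either route needs almost everyone to re-present.

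**4. The 121.8 days.** At the stated ratio, 73.5/0.66 = 111.4 days. With 0.66 and no censoring, the method in step 3 gives 31.4/(ln 0.66)² ≈ 182 events, 91 per arm, × 1.1 = 100.1, rounded up to 101 per arm, or 202.

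**5. Power on the 15% basis, 12-month horizon.** The Intervention proportion is 1 − 0.85^HR: 10.17% at 0.66 and 9.34% at 0.603. Events E = n per arm × (sum of the two proportions). Power = Φ(√E × |ln HR|/2 − 1.96). The 10% adjustment is applied by dividing E by 1.1.

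For 796 patients at HR 0.66: E = 398 × (0.15 + 0.1017) = 100.2. Unadjusted, Φ(10.01 × 0.2078 − 1.96) = Φ(0.12) = 55%. Adjusted, E = 91.1 and Φ(0.02) = 51%.

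| Patients | TAU at 12 months | HR | Events | Power, unadjusted | Power, with 10% adjustment |
|---|---|---|---|---|---|
| 796 | 15% | 0.66 | 100 | 55% | 51% |
| 796 | 15% | 0.603 | 97 | 70% | 66% |
| 796 | 12% | 0.66 | 80 | 46% | 43% |
| 796 | 25% | 0.66 | 168 | 77% | 73% |
| 138 | 15% | 0.66 | 17 | 14% | 13% |

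**6. Patients needed for 80% at HR 0.66 and 15%.** 182/[(0.15 + 0.1017)/2] ≈ 1,447, or about 1,591 after × 1.1.

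**The case against.** **The trial does not enrol 138.** The stated requirement is 796, so the 13–14% power at 138 describes a trial nobody plans. This stands. A reader might infer that the study is too small by a factor of ten; the documents do not support that, and the size of the problem has to be judged at 796.

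**796 may already reflect the 15%.** With a 4.3-year median, HR 0.66, 24 months of accrual and every patient followed to the end of a three-year calendar study, log-rank formulas need about 787–813 patients before inflation. At 796 that design gives about 185 events and 81% power (77% with the adjustment). The match is suggestive, but the text attaches 796 to an incidence rate ratio, and the stated endpoint stops at 12 months. It therefore does not rescue the endpoint as defined. It does show that the 51–55% depends on the 12-month cut-off.

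**Power is better at the ratio the medians imply.** At 0.603 it is 66–70% at 15% repetition, and it passes 80% (87–90%) only if repetition is also 25%. Neither is the protocol's base assumption.

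**73.5 days may be a median among repeaters.** That is plausible, and a reader might take it as established. The protocol does not say so; it calls the figure the median in the usual care group, and the cited source is not at hand. If it were so, 138 would count patients with events rather than patients to randomise, and the stated requirement would still be wrong.

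**The ratio comes from event rates.** The Background reports that a meta-analysis "found a non-significant benefit for any episode of repeat DSH (binary outcome) and a significant benefit for repetition event rates", so a reader might call 0.66 for first events an error. It is not shown to be one. The assumption is made openly, and the non-significant result is for a binary outcome in studies described as generally underpowered. This is a question of plausibility and forms no part of the point.

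**Conclusion.** The point holds, and the passage is wrong as written. The two TAU medians cannot both be true, 121.8 days does not follow from 0.66, and 80% power with 138 patients is not supported by the protocol's own 15%. Nothing elsewhere in the article reconciles them.

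The consequence is a 12-month power at the planned 796 of about 51% at HR 0.66 with the protocol's adjustment (range 43–73% over 12–25% repetition), or 55% (46–77%) without it. These figures rest on a two-sided 5% test, proportional hazards, complete 12-month follow-up and a simple 10% discount of events for clustering.

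The article nowhere says that this endpoint is amply powered; that is only what a comparison of 138 with 796 might suggest. The error does not undermine the event-rate calculation behind 796, which was not under test here.

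**What to change.** In the Sample size calculation section, remove the 73.5/121.8-day calculation and the 138. Base the time-to-first-event statement on 15% re-presenting by 12 months, and give the 12-month power of 398 per arm at HR 0.66 with the 10% adjustment: about 51%, with 43–73% across 12–25% repetition.

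If the source shows that 73.5 days is a median among repeaters only, say so, and say that it cannot serve as the median for all randomised patients.

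The change is to wording in one section. Enrolment, endpoint and analysis stay as they are. The cost is a less favourable power figure for a primary endpoint.

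### The 138-patient requirement for time to first re-presentation rests on a 73.5-day TAU median that contradicts the 4.3-year median and 15% rate in the same paragraph; 138 patients give about 14% power, not 80%

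*Protocol article*

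**What the plan says.** All the sizing is in one paragraph of the protocol article, under Sample size calculation.

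- For TAU it says: "We have also assumed a median survival time (time to first repetition) in the TAU condition of 4.3 years". The basis follows: "Currently ~ 15% in the usual care group who present for DSH re-present within the following 12-months, or a probability of survival of 0.85".
- It then sizes the comparison of median time to first repetition with a different TAU median, "assuming a median survival time in the usual care group of 73.5 days [12". The effect is carried over from the event-rate calculation, a ratio of 0.66.
- On that basis it puts the Intervention median at 121.8 days, a difference "which requires a total sample size of 138 participants/subjects", that is 69 per arm, at 5% significance and 80% power with a 10% adjustment for correlation within hospitals.

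The Background section gives the literature rate: "Repetition of DSH within 1 year of hospital admission occurs at a median proportion of 15% (interquartile range 12–25" per cent. Time to first re-presentation is hypothesis 2 under Aims and hypotheses, and a primary endpoint assessed at 6 and 12 months under Outcome measures. The trial's overall target, set by the event-rate endpoint, is 796.

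**The concern.** Both medians are given for usual care and for time to first repetition, and they differ about 21-fold (4.3 × 365.25 / 73.5 = 21.4). Nothing in the text limits the shorter one to a subgroup. A 73.5-day median means that half of TAU patients have re-presented by day 73.5. Whatever the shape of the hazard, that cannot coexist with 15% re-presenting by day 365.

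The choice matters because a survival comparison draws its power from events. If nearly everyone has an event, the number of patients needed is close to the number of events needed. If 10–15% have one, it is about eight times the number of events.

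The 138 is the only sample size the protocol states for this endpoint. It tells the reader that 796 is almost six times what is needed (796/138 = 5.8). A null result on time to first re-presentation could then be taken as strong evidence of no effect when the trial may be underpowered for it.

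**Working it through.** **Inputs.** From Sample size calculation: TAU 12-month proportion 15%; TAU median 4.3 years or 73.5 days; Intervention median 121.8 days; RR 0.66; 5% significance; 80% power; 10% adjustment; 69 per arm; 796 in total. From Study design: 24 months of recruitment and 12 months of follow-up. Assumptions: two-sided testing (the article does not say, and one-sided versions do not reproduce 138), 1:1 allocation, and a constant hazard as in the protocol's own 4.3-year calculation.

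**1. The two medians**

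- From 15% at 12 months: ln(0.5)/ln(0.85) = 4.27 years. This matches the stated 4.3.
- From 73.5 days: 1 − 0.5^(365/73.5) = 0.968 of TAU patients re-present within a year.
- From 121.8 days: 1 − 0.5^(365/121.8) = 0.875 in the Intervention arm.

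**2. Reproducing the 138**

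The printed medians imply a hazard ratio of 73.5/121.8 = 0.603. Schoenfeld's formula gives the events as 4(1.960 + 0.842)²/(ln HR)² = 4 × 7.849/(ln 0.603)² = 123.1. Two routes then lead to 138:

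- Every patient has an event: 62 per arm, 62 × 1.1 = 68.2, rounded up to 69 per arm, total 138.
- Exponential survival at the printed medians, uniform accrual over 24 months and a further 12 months of follow-up: 125.2 patients, × 1.1 = 137.7, so 138. About 98% of patients have an event (123.1/125.2).

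The article does not say which was used. Both need an event in all or nearly all patients. A fixed 12-month window at the same medians gives 133.6 × 1.1 = 146.9, which does not match.

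**3. What 138 patients deliver at 15%**

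With HR 0.66 the Intervention proportion is 1 − 0.85^0.66 = 0.1017.

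- Expected first events: 69 × (0.15 + 0.1017) = 17.4.
- Power: Φ(|ln 0.66| × √(17.4/4) − 1.96) = Φ(0.4155 × 2.084 − 1.96) = Φ(−1.094) = 0.137.

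| TAU 12-month proportion | HR | First events in 138 | Power |
|---|---|---|---|
| 12% | 0.66 | 13.9 | 11.8% |
| 15% | 0.66 | 17.4 | 13.7% |
| 25% | 0.66 | 29.2 | 20.1% |
| 15% | 0.603 | 16.8 | 17.7% |

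The 12% and 25% rows use the interquartile range quoted in the Background. The design assumption is 15%. No clustering adjustment is applied here; with it, the 13.7% becomes 12.8%.

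**4. What 80% power needs at 15%**

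- HR 0.66: 4 × 7.849/0.4155² = 181.8, so 182 events. Patients: 181.8/[(0.15 + 0.1017)/2] = 1,445; × 1.1 = 1,589.
- HR 0.603: 123.1 events, 1,011 patients; × 1.1 = 1,112.

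**5. What the planned 796 deliver at 15%**

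- HR 0.66: 398 × 0.2517 = 100.2 first events, power 55%, or 51% after dividing the events by 1.1.
- HR 0.603: 96.9 first events, power 70%, or 66% after the adjustment.

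**6. Separate from the 121.8-day figure**

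With RR 0.66 the Intervention median should be 73.5/0.66 = 111.4 days, not 121.8. Correcting only that gives 91 events per arm, 91 × 1.1 = 100.1, rounded up to 101 per arm, total 202 (other routes give 200–221). At 15%, 202 patients yield 101 × 0.2517 = 25.4 first events and 18% power. The main fault is the 73.5-day median, not the ratio.

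**The case against.** The strongest reply is that nobody plans a trial of 138. Enrolment is set at 796 by the event-rate endpoint, so 14% power describes a hypothetical trial, and the figure that matters is the power at 796. That is right as to consequence: the harm is false assurance, not a trial of the wrong size. It does not rescue the statement, which is the only sizing given for a primary endpoint. At 796 the power is still only 51–55% at the protocol's own rate and effect, which the 138 conceals.

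Three narrower points stand in part.

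- How the authors reached 138 is not documented. One route treats every patient as having an event, the other about 98% of them. The difference does not affect the conclusion.
- That 73.5 days describes only patients who re-presented is an inference. It is the natural reading, since the figure cannot describe all TAU patients at a 15% rate, but the cited source is not at hand. If it is correct, 138 is in effect a number of repeaters, and 796 patients would supply only about 100.
- The requirement depends on the hazard ratio. With the adjustment it is about 1,590 at 0.66 and about 1,110 at the printed ratio of 0.603. Either is at least eight times 138.

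It is also fair to say that readers of the results will look at the hazard ratio and its interval rather than at the 138, so misreading of a null result is a risk, not a certainty.

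**Conclusion.** The concern holds. One paragraph uses two incompatible TAU medians for the same variable, and the sample size for the second primary endpoint is built on the one that contradicts the protocol's 15% rate. At 15% and a hazard ratio of 0.66, 138 patients have 13.7% power against the stated 80%. Across 12–25% re-presentation at that ratio power is 12–20%, and at 15% with the printed ratio of 0.603 it is 18%.

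These power figures assume a constant hazard, a two-sided 5% test and 12 months of follow-up for every patient. The contradiction between the medians needs none of these assumptions. The 796 target does not rest on the 138, so what must change is the claim about power for this endpoint.

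**What to change.** Delete the 73.5-day and 121.8-day medians and the 138. Size the endpoint from the 15% proportion (4.3-year median) already in the paragraph, and state the requirement in events. Wording along these lines would do:

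> With 15% of TAU patients re-presenting within 12 months and a hazard ratio of 0.66, 80% power at two-sided 5% needs 182 first events, about 1,445 patients (about 1,590 with the 10% adjustment). The planned 796 patients are expected to yield about 100 first events and about 55% power (51% with the adjustment).

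If 73.5 days is kept as background, confirm from the source that it is the median among patients who re-present, label it so, and do not size from it.

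The cost is two rewritten sentences and a less favourable stated power for the second primary endpoint. The correction itself needs no extra patients. Accepting that power or enlarging the trial is then an open decision for the sponsor.

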## Methods/design

### Aims and hypotheses

The aim of this study is to investigate whether Treatment As Usual (TAU) aftercare for DSH patients plus supportive SMS text messages delivered over 1 year reduce DSH re-presentations to hospital, compared to TAU alone. Our hypotheses are: 1) SMS text messages *plus* TAU will be associated with a significantly lower incidence event rate of hospital DSH re-presentations, compared to the patient group receiving TAU; and 2) SMS text messages *plus* TAU will be associated with a significantly greater time to first hospital DSH re-presentation compared to TAU.

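### Time to first re-presentation is sized with a rate ratio borrowed from total event counts, and the stated 80% power is not delivered at the planned 796 patients and 15% risk

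*Protocol article*

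**What the plan says.** The protocol article lists time to first re-presentation as a primary endpoint (Outcome measures) and gives it its own hypothesis, a "significantly greater time to first hospital DSH re-presentation compared to TAU" (Aims and hypotheses). Statistical methods assigns it multi-level Cox models and clustered log-rank tests. The event-count endpoint gets multi-level negative binomial regression.

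The Sample size calculation section opens with "Assuming an incidence rate ratio (based on event rates) of RR = 0.66" and reaches 796 patients, 398 per arm. For time to first repetition it takes the same ratio, "a similar relative difference in event rates between Intervention and TAU conditions as above (RR = 0.66"). It proceeds by "assuming a median survival time in the usual care group of 73.5 days", from which "the estimated median survival time in the Intervention condition is 121.8 days". The result is 138 patients in total, "with 5% significance and 80% power, and 10% adjustment for correlation of individuals within hospitals".

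The same section says that about 15% of usual-care patients re-present within 12 months, and converts this to a median of 4.3 years.

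On prior evidence, the Background reports that a meta-analysis of brief contact interventions "found a non-significant benefit for any episode of repeat DSH (binary outcome) and a significant benefit for repetition event rates".

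**The concern.** An event-rate ratio and a first-event hazard ratio are different quantities. The first counts all re-presentations, so a few patients with many episodes can drive it. The second uses one event per patient. If patients differ in their underlying rate, a given reduction in total events produces a smaller relative reduction in first events. The planned negative binomial model is the usual choice when patients do differ in this way. Carrying 0.66 across without argument is therefore an optimistic assumption.

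The section also makes this endpoint look the easier of the two, needing 138 patients against 796. A reader would conclude that 796 patients give it ample power. If they do not, a non-significant result on a primary endpoint could be read as evidence against the messages when the trial could not settle the question.

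**Working it through.** **Inputs from the Sample size calculation section.** RR 0.66; medians of 73.5 and 121.8 days; 5% significance; 80% power; 10% clustering adjustment; 138 and 796 patients; 15% control risk at 12 months. Sidedness is not stated; two-sided is assumed.

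**1. Reproducing 138.** The medians imply HR = 73.5/121.8 = 0.603. Schoenfeld's formula gives events = 4(1.96 + 0.8416)²/(ln HR)² = 31.396/0.5051² = 123.1, rounded up to 124, or 62 per arm. If every patient has an event, 62 × 1.1 = 68.2, so 69 per arm and 138 in total. This matches exactly. One-sided versions give 108 to 114 and do not match.

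**2. The same calculation at 0.66.** 73.5/0.66 = 111.4 days, not 121.8. Events = 31.396/0.4155² = 181.8, so 182, and the total is about 202. At HR 0.66 the 124 events behind the printed figure give 64% power.

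**3. The two control medians.** With exponential times, a 73.5-day median means 1 − 0.5^(365/73.5) = 97% re-presenting within 12 months. The section states 15%, for which the median is ln(0.5)/ln(0.85) = 4.27 years, the printed 4.3.

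**4. Power at 796 patients and 15% risk.** Under proportional hazards the intervention risk is 1 − 0.85^HR. Events = 398 × (0.15 + intervention risk). Power = Φ(½√events × |ln HR| − 1.96). For the clustering adjustment, events are divided by 1.1. The documents give no first-event HR, so every row below 0.66 is an assumption.

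| First-event HR | Intervention risk | Events | Power | Power after 10% adjustment |
|---|---|---|---|---|
| 0.66 | 10.2% | 100 | 55% | 51% |
| 0.75 | 11.5% | 105 | 31% | 29% |
| 0.80 | 12.2% | 108 | 21% | 20% |
| 0.85 | 12.9% | 111 | 13% | 13% |
| 0.90 | 13.6% | 114 | 8% | 8% |

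The HR detectable with 80% power is about 0.56 before the adjustment.

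**5. How far a rate ratio of 0.66 shrinks for first events.** Let patients' rates follow a gamma distribution with shape k, so that counts are negative binomial and P(no event) = (1 + μ/k)^(−k). Choose μ so that the control risk is 15%, multiply it by 0.66, and compare 12-month cumulative hazards of a first event. The values of k are assumptions; the article gives no dispersion.

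| k | Control mean μ | Intervention first-event risk | Implied first-event HR |
|---|---|---|---|
| 0.5 | 0.192 | 10.7% | 0.70 |
| 0.2 | 0.251 | 11.4% | 0.74 |
| 0.1 | 0.408 | 12.2% | 0.80 |

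With no heterogeneity the ratio stays at 0.66.

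**The case against.** Three stronger readings are tempting, and the article does not support them.

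- *A reader might infer that the stated power belongs to another test.* Step 1 shows that it does not: 138 is a log-rank calculation on first-event medians. Only the effect size is borrowed, and the value actually used is 0.603.
- *A reader might infer from the Background that brief contacts do not affect first events, or that a null result here is likely.* The text reports a benefit that was non-significant, gives no estimate for either outcome, and adds that the studies generally lacked power. One significant and one non-significant result do not show that two effects differ. The pattern is consistent with attenuation and does not prove it.
- *A reader might judge the endpoint by its power with 138 patients.* The trial requires 796, so 138 does not describe it.

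It can also be said that much of the shortfall comes from the event fraction and not from the carry-over. That is right: at 15% risk, power is already 55% with 0.66 fully granted. With the 73.5-day median and 796 patients, adjusted power would be 96% at HR 0.75 and 83% at 0.80. But that median implies 97% re-presenting within a year, which the same section contradicts. Only the 15% figure describes the proportion of all usual-care patients who re-present within the trial's follow-up period.

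Finally, the size of the attenuation depends on a dispersion that the article does not give. This limits how precisely the loss can be stated. It does not supply the missing justification for 0.66.

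**Conclusion.** The point holds in this form: a primary endpoint is sized with an effect taken from total event rates, no first-event hazard ratio is stated or justified, and the printed inputs are mutually inconsistent. The claim of 80% power fails at 796 patients and 15% risk even on the favourable assumption that 0.66 carries over in full (55%, or 51% adjusted). Any attenuation makes it worse.

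The 55% rests on the protocol's 15% risk, proportional hazards and a two-sided 5% test. The lower figures rest in addition on an assumed range of hazard ratios. This is a fault in the stated power and in how a result would be read. It does not invalidate the endpoint or the sizing on event rates; the 796 itself cannot be checked, because no control event rate or dispersion is given.

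**What to change.** In the Sample size calculation section:

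1. Remove the carry-over of 0.66 to time to first re-presentation, and the statement that 138 patients give 80% power.
2. Reconcile the medians: 121.8 days with the ratio of 0.66, and 73.5 days with the 15% risk and the 4.3-year median.
3. State power for time to first re-presentation at 796 patients and 15% risk, over a declared range of first-event hazard ratios. The table in step 4 of the working would serve. If one hazard ratio is preferred, justify it from first-event data.
4. Say that the trial is sized on the event-rate endpoint and that time to first re-presentation has lower power, so a non-significant result on it is inconclusive. That wording does not excuse a failed endpoint in advance.

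The cost is a few sentences and a small table, with no extra patients. The drawback is that the stated power for the second primary endpoint becomes visibly less favourable.
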